## Abstract

**Background:**

The protection and promotion of breastfeeding is considered a priority in Europe where only 22% of infants less than 6 months old are exclusively breastfed. In Spain this percentage reaches 24.8% but in our city it falls to 18.26%. Various studies emphasise that the improvement of these results should be based upon the training of health professionals. Following the recommendations of a breastfeeding guide can modify the practice of health professionals and improve results with respect to exclusively or predominatly breastfed children at 6 months of age.

**Method/Design:**

This study involves a community based cluster randomized trial in primary healthcare centres in Leganés (Madrid, Spain). The project aims to determine whether the use of an implementation strategy (including training session, information distribution, opinion leader) of a breastfeeding guideline in primary care is more effective than usual diffusion.

The number of patients required will be 240 (120 in each arm). It will be included all the mothers of infants born during the study period (6 months) who come to the health centre on the first visit of the child care programme and who give their consent to participate. The main outcome variable is the exclusive o predominant breastfeeding at 6 moths of age..

Main effectiveness will be analyzed by comparing the percentage of infants with exclusive or predominant breastfeeding at 6 months between the intervention group and the control group. All statistical tests will be performed with intention to treat. Logistic regression with random effects will be used to adjust for prognostic factors. Confounding factors or factors that might alter the effect recorded will be taken into account in this analysis.

**Discussion:**

Strategies need to be found which facilitate the giving of effective advice on breastfeeding by professionals and which provide support to women during the breastfeeding period. By applying the guide's recommendations, clinical variability can be reduced and the care received by patients can be improved.

**Trial registration:**

The trial was registered with ClinicalTrials.gov, number NCT01474096

## Background

### Current breastfeeding situation

The World Health Organization (WHO) considers breastfeeding the ideal way to feed infants, as it provides them with the nutrients needed for adequate growth and development, recommending exclusive breastfeeding until 6 months [1] and its continuance in supplemented form until 2 years of age [2].

Nowadays efforts are being made in both health and non-health areas for promoting the initiation and continuation of breastfeeding. Its benefits as much to the mother as to the infant, are widely known and it is thought to be an important factor in the promotion of children's health [3-6]. In spite of this, breastfeeding statistics are far from the levels considered adequate by the WHO, which estimates that 97% of women of fertile age are able to breastfeed their children.

In the latest *The State of the World's Children Report*, published in 2007 by the United Nations Children's Fund (UNICEF), it is noted that breastfeeding figures in Europe are discouraging (22% exclusive breastfeeding in infants less than 6 months old) [7]. In our country there is no official record system to make available data on the tracking and monitoring of breastfeeding. According to information from the latest *National Survey of Health*, in Spain breastfeeding at 6 months of age is 24.72% and in Madrid 23.54% [8]. In the study undertaken by the Spanish Paediatrics Association it is concluded that the average length of breastfeeding in Spain is about 3 months and only 24.8% of infants are breastfed at 6 months of age [9]. The data which has been obtained from existing records of computerised health reports in Primary Healthcare centres (PHCC) in our city show us a rather more unfavourable panorama as the percentage of 18.26%.

The WHO enumerated "*Ten Steps Towards Happy and Natural Breastfeeding" *[10] which are the basis for the introduction of projects based on the Baby Friendly Hospital Initiative (BFHI) which establishes an integrated approach to increase breastfeeding and has shown very positive results according to some studies [11,12].

### The role of health professionals

The protection and promotion of breastfeeding has been considered a priority in Europe, establishing the training of health professionals who must give such advice as one of the aspects upon which it should be based. The development of training systems which give professionals the knowledge, skills and attitudes required for the management of breastfeeding is considered necessary [13], since it has been seen the role of health professionals in breastfeeding rates [14].

Training in breastfeeding management is normally a shortfall in the undergraduate training of health professionals; this results in a lack of knowledge of the subject which has been made clear in many studies [15-17]. This shortfall in training persists even in the case of professionals with more specialist post-graduate training in this area. Thus, in the study undertaken by Temboury [15] on breastfeeding knowledge possessed by paediatric interns throughout Spain, using a self-completed questionnaire, it was concluded that there are important gaps in knowledge. It is noteworthy that the results differ from province to province, a fact which the researchers attribute to the different training plans and activities to improve breastfeeding which have been put into practice with institutional support in each province.

Akuse et al. [16] surveyed health and non-health professionals and found that although breastfeeding is thought of as highly important, a large percentage of health professionals tended to systematically recommend supplements for baby-feeding unnecessarily. The majority of the health professionals had received undergraduate training on the subject, but only a third had received specific training on the clinical approach to breastfeeding, something considered indispensable in clarifying such concepts.

In the study by Smale et al. [17], a qualitative investigation was undertaken with interviews and discussion groups. The results show that many health professionals do not feel able to give suitable support to breastfeeding mothers, consider that they receive little specific training in breastfeeding and feel that what they do receive refers above all to the anatomy, physiology and benefits of breastfeeding, but not to the tools needed to tackle the problems which can present themselves during breastfeeding.

Support by professionals has beneficial effects on the length of the breastfeeding, and the setting up of training projects has resulted in the improvement of breastfeeding indicators in the places where they have been developed. This confirms the fact that the training of professionals is closely linked to the commencement and continuance of breastfeeding. Travers et al. [18] found that some practices and opinions of paediatricians and nurses, such as not considering important the recommendations with regard to the duration of breastfeeding or the giving of adapted formula supplements to infants showing no gain in weight, were related to the probability of exclusive breastfeeding being continued or not.

For all these reasons the education and continuing training of health professionals working in Primary Care so that they acquire the necessary competence to suitably orientate mothers is a priority [19].

There are numerous strategies which can be employed on health professionals in order to encourage the promotion of breastfeeding. In a revision by Cochrane which evaluates the effectiveness of different breastfeeding support schemes [20], it is concluded that additional professional support is effective in prolonging breastfeeding and that the training courses for professionals recommended by the WHO are an efficient strategy for training health professionals. In a study undertaken in the Malaga Hospital [21], in which training courses for professionals as well as other community activities to promote breastfeeding were carried out, an increase took place in the length of breastfeeding in mothers who had given birth by caesarean section. In addition, the WHO and UNICEF have proposed the use of some training techniques to improve this situation [22]. They state the need for health professionals to have specific training on breastfeeding counselling in courses between 20 and 40 hours in length and, in the same way, health service administrators should attend 12-hour courses, with the intention of correcting the gaps in knowledge which currently exist.

### Guideline implementation strategies

In Madrid in the public health system, the Child Care Programme. (0-14 years old) is carried out in Primary Care. Within the framework of this programme, periodic visits are made to the nursing clinic and/or to the paediatrician for health examinations or for health education. In our city, taking into account the low level of exclusive breastfeeding at 6 months of age, the efforts which are made by the programme to promote breastfeeding are thought to be insufficient. For this reason it has been developed a breastfeeding action guide in coordination between Primary Care and the maternity hospital.

The adoption by health professionals of the recommendations included in the guide and their application to their patients means a process of change in clinical practice and, as such, is complex and depends on multiple factors [23]. It is essential that professionals involved participate both in their distribution as well as in the implementation strategies that are contemplated.

Whatever the implementation strategy, it should have an impact at four levels: increasing the knowledge of health workers and patients; changing attitudes, habits and behaviour of professionals in their clinical practice; taking into account also patients' preferences and administrative and economic influences; and modifying results, which signifies improving the quality of medical assistance and finally the health of the population by compliance with the recommendations of the Practice Guideline [24,25].

There exist various strategies for the implementation of practice guidelines which have shown their efficiency.

The Cochrane group EPOC (Effective Practice and Organization of Care) suggests they be classified in four categories: professional interventions (such as distribution of educational materials or educational meetings); financial interventions (such as fee-for-service or prospective payment); organisational interventions (such as creation of clinical multidisciplinary teams); and regulatory interventions (any intervention that aims to change health services delivery or costs by regulation or law) (EPOC Data Collection Checklist 2009) [26].

The revision by Grimshaw et al. [27] evaluates the effectiveness and cost of different organizational strategies for the dissemination-implementation of practice guidelines. It stands out that the majority of implementation strategies improve adherence to the practice guidelines. Simple strategies like checklists increase adherence by 14.1%. The distribution of educational materials increases it by 8.1%. Educational programmes, almost always as components of more complex interventions, improve practice by 6%, and audit inspections and feedback by 7%. In their conclusions it is pointed out that there is scarce evidence on which strategies are the most effective in each situation, for which reason the authors consider necessary the development and validation of theoretical models of behaviour change, as well as investigation of the efficiency of the strategies given the presence of different obstacles and factors which may modify effectiveness.

Without doubt, to achieve this change in health professionals demands that intervention strategies be realistic and adapted to each context. We consider essential the introduction of organizational strategies which allow us to generalise the use of the guide and the application of its recommendations as well as to measure and evaluate the impact which the implementation of the practice guideline may have both on professionals, modifying their practice, and on patients, improving their health results [28,29].

Our investigation proposal is based on the premise that we will be able to reach all health professionals involved in the care of mothers and infants by doing the training on site in their Primary Healthcare Centre (PHCC). By evaluating the effectiveness of this type of intervention we will be able to produce rigorous continuous training plans and, even more importantly, be able to know the results for the patient. For all these reasons we think it essential to know which strategies are the most suitable for the integration to take place in an effective way. Because we consider inevitable a 'contamination' effect of influence on each other between professionals working in the same centre, a cluster design has been chosen so that the interventions which do or do not take place will include all the professionals in each PHCC.

## Hypothesis

The implementation of a breastfeeding guideline, with the additional support of training and information directed at the professionals who impart the care, implies a greater integration of the guide's recommendations in usual clinical practice. As a result of this integration, an increase in the percentage of breastfed infants and a greater duration of breastfeeding will be produced.

The proportion of infants using exclusive breastfeeding (EBF) or predominant breastfeeding (PBF) at six months will increase at least 20% with respect to the control group (38% for the intervention group compared with 18% for the control group).

## Objectives

The aim of the present work is to determine whether an implementation strategy for a breastfeeding guide is more effective than the usual diffusion in terms of increasing the percentage of infants using EBF or PBF at 6 months.

Secondary objectives:

To determine whether an implementation strategy for a breastfeeding guide is more effective than the usual diffusion in terms of increasing the percentage of infants using EBF or PBF at 1, 3 and 12 months.

To determine whether an implementation strategy for a breastfeeding guide is more effective than the usual diffusion on duration of EBF and PBF.

To evaluate knowledge on breastfeeding possessed by health professionals prior to undertaking the intervention.

Describe the reasons for withdrawal from breastfeeding in both groups.

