### Sample size

For an alpha of 0.05, a power of 80%, and in order to detect an increase of 20% in the percentage of exclusive or preferential breastfeeding at 6 months of age in the intervention group, the overall sample size required is 176 patients (88 in each arm of the study).

Since randomisation is by clusters, the sample size has to be larger than if simple randomisation is performed, in order to take into account the design effect. The intra-class correlation coefficient is 0.01 [30] and a mean cluster size is assumed to be 30 patients. The design effect is 1.29. Given these assumptions, and expecting a 5% loss rate at one year, the final sample size required is 240 (120 patients in each arm).

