### Statistical Analysis

The use of randomisation by clusters conditions the statistical analysis that can be employed, especially in the calculation of confidence intervals and the testing of hypotheses. The following analyses will be undertaken:

Descriptive analysis of each variable with its corresponding CI at 95%. Description of the profile of patients who abandon the study plus their reason for withdrawal.

Comparison of the group at the beginning of the trial with regards to response variables, descriptive variables, and prediction factors. Bivariate statistical tests will be used suitable to the type of variable (qualitative or quantitative).

Analysis of primary outcome. There will be a comparison of the percentage of infants using EBF or PBF at 6 months in the two study arm using the Chi-squared test and the calculation of confidence intervals.

Logistic regression with random effects will be used to adjust for prognostic factors. Confounding factors or factors that might alter the effect recorded will be taken into account in this analysis.

To assess the effect of the intervention on the duration of the various types of breastfeeding, a survival analysis will be used comparing the two groups using the log-rank test. The control of potential confounding variables will be performed by the construction of various Cox regression models.

Effect of the intervention on secondary outcome variables: comparison of the proportion the percentage of EBF or PBF at 1, 3 and 12 months using the Chi-squared test and the calculation of confidence intervals.

All statistical tests will be performed with intention to treat. The last observation carried forward will be used for missing data. Significance will be set at P < 0.05. All calculations will be made using SPSS^© ^v.18 software.

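### The 12-month secondary outcome (EBF or PBF) does not measure what the cited feeding standard calls for at that age, and no listed outcome measures any breastfeeding then

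*Protocol article*

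**What the plan says.** In the Protocol article, the primary outcome is exclusive (EBF) or predominant (PBF) breastfeeding at 6 months. The Objectives section extends the same composite to other ages; the secondary aim is stated as "increasing the percentage of infants using EBF or PBF at 1, 3 and 12 months". Statistical Analysis fixes the test for this aim, comparing "the percentage of EBF or PBF at 1, 3 and 12 months using the Chi-squared test" with confidence intervals. A further objective covers the duration of EBF and PBF.

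The Background (Current breastfeeding situation) describes WHO as "recommending exclusive breastfeeding until 6 months [1] and its continuance in supplemented form until 2 years of age".

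Under Data collection method, calls are planned at 1, 3, 6 and 12 months. At each call the mother is asked whether the infant is breastfed at that time and, if not, when and why breastfeeding stopped. Missing data are handled by last observation carried forward (LOCF).

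**The concern.** The composite suits ages up to 6 months, when the cited standard is exclusive breastfeeding. After 6 months the same standard expects breast milk plus other food. At 12 months the objective thus asks for an increase in a feeding state that the standard expects infants to have left.

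Two things are at stake. First, a difference at 12 months, in either direction, could not be read as better or worse uptake of the recommendation. Second, the Hypothesis section predicts more breastfed infants and longer breastfeeding. The natural 12-month measure of that is whether the infant is still breastfed at all, and this is not a listed outcome. A real gain in continued breastfeeding after 6 months could go without a planned test.

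**Working it through.** **Step 1: the sections side by side.**

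- Standard (Background): exclusive to 6 months, supplemented from then to 2 years.
- Objective and test (Objectives, Statistical Analysis): a higher proportion on EBF or PBF at 12 months counts as benefit.
- For EBF the conflict is direct, because a supplemented infant is not exclusively breastfed.
- For PBF it depends on the definition. If PBF excludes formula and solids, the conflict covers the whole composite. If it means mainly breast milk, some infants fed to the standard could still count.

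**Step 2: reproduce the plan's sample size.** Inputs: "38% for the intervention group compared with 18% for the control group" (Hypothesis); alpha 0.05, power 80%, intra-class correlation 0.01, mean cluster size 30 and 5% loss (Sample size). Two-sided alpha is assumed, as sidedness is not stated.

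- Uncorrected n per arm = [1.960 × √(2 × 0.28 × 0.72) + 0.842 × √(0.18 × 0.82 + 0.38 × 0.62)]² / 0.20² = 78.
- With continuity correction: 88 per arm, 176 in total, as stated.
- Design effect = 1 + (30 − 1) × 0.01 = 1.29, as stated.
- 88 × 1.29 / 0.95 = 119.5, so 120 per arm and 240 in total, as stated.

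**Step 3: power at 12 months.** The article gives no 12-month rate, so a range is assumed. The intervention rate is taken as the control rate × 38/18, which carries the planned 6-month ratio forward. Pairs remaining per arm: 120 × 0.95 = 114. Effective number: 114 / 1.29 = 88, assuming the same intra-class correlation at 12 months. Power is the exact binomial power of the uncorrected Pearson test at two-sided 0.05.

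| Control rate (assumed) | Intervention rate | Expected cases of 114 (control v intervention) | Power |
|---|---|---|---|
| 0% | 0% | 0 v 0 | 0 |
| 0.5% | 1.1% | 0.6 v 1.2 | 1% |
| 1% | 2.1% | 1.1 v 2.4 | 5% |
| 2% | 4.2% | 2.3 v 4.8 | 12% |
| 3% | 6.3% | 3.4 v 7.2 | 16% |
| 5% | 10.6% | 5.7 v 12.0 | 27% |
| 10% | 21.1% | 11.4 v 24.1 | 53% |
| 18% (6-month plan) | 38% | 20.5 v 43.3 | 85% |

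With a control rate of 1%, the intervention rate would have to be about 11% for 80% power (normal approximation).

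Two points make low rates plausible without establishing them. EBF or PBF that has ended does not normally resume, so the planned 18% and 38% at 6 months act as ceilings. The Background also reports that "the average length of breastfeeding in Spain is about 3 months".

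**Step 4: the LOCF contribution.** Losses at 5% are 120 × 0.05 = 6 per arm. If all six were last seen at the 6-month call (the upper limit), carrying that status forward adds 6 × 0.18 = 1.1 control cases and 6 × 0.38 = 2.3 intervention cases. At a true control rate of 1%, genuine cases are 1.1 and 2.4, so the two sources are about equal. At 2% they are 2.3 and 4.8, so carried-forward cases number about half the genuine ones. The artefact is larger in the intervention arm.

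**The case against.** The strongest reply is that PBF is undefined. The Sample size section calls the outcome exclusive or *preferential* breastfeeding, and the list of maternal variables uses exclusive, preferential and partial. If preferential means mainly breast milk, an infant receiving some supplements at 12 months might still qualify, and a higher value would not be a departure from the standard. This stands. A reader might infer that perfect adherence gives 0% on the composite, but the article supports that for EBF only.

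The standard is WHO's, cited as background. The local guide under test is not shown, so what it says about feeding after 6 months cannot be checked. This also stands. The article still offers no other standard that would make EBF or PBF at 12 months a target.

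Secondary outcomes need not be powered, and handling of sparse tables can be left to an analysis plan. That is fair: low power alone would not be a finding. It matters here because the outcome is also the wrong one for the age.

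Statistical Analysis speaks of the duration of various types of breastfeeding, which may already include any breastfeeding. Perhaps so, but Objectives names only EBF and PBF duration, so the intention is not settled.

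The call asks simply whether the infant is breastfed, so any breastfeeding may have been meant all along. If so, Objectives and Statistical Analysis still say something else and need correcting.

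**Conclusion.** The point holds as a mismatch between a secondary outcome and the standard the protocol cites. At 12 months, EBF or PBF does not measure adherence to that standard. This is certain for EBF and conditional on the definition for PBF. No listed outcome measures any breastfeeding at that age.

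The size is conditional. Power is about 0 to 27% for assumed control rates of 0 to 5%, and 53% at 10%, given the 38/18 ratio, the 1.29 design effect and 5% loss.

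Two stronger readings are tempting and go beyond the document. One is that the outcome is known to be near zero in both arms; no 12-month rate is given. The other is that any non-zero result would be mostly carried-forward 6-month status. Even at the upper limit for LOCF, carried-forward cases only match the genuine ones at a 1% control rate and are outnumbered by them at 2%.

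The effect is confined to one time point of one secondary objective. The 6-month primary outcome and the sample size of 240 are untouched.

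**What to change.** - In Objectives and Statistical Analysis, keep EBF or PBF at 1 and 3 months as secondary outcomes, with 6 months as primary.
- Replace the 12-month secondary outcome with any breastfeeding at 12 months. Report EBF or PBF at 12 months descriptively only.
- In both sections, name duration of any breastfeeding to 12 months explicitly among the durations analysed.
- State the definition of PBF, so that readers can tell whether a supplemented infant can count.

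The cost is wording in two sections and one definition. No new data are needed: the planned calls already ask whether the infant is breastfed and record the date of stopping. The sample size does not change.
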